### Aim and Objectives

The aim of the study is twofold: (1) to evaluate a relapse prevention treatment for patients with problem gaming and internet gaming disorder recruited from child and youth psychiatry clinics across southern Sweden (Region Skåne) and (2) to test whether the quality of parent-child relationships plays a role for the effect of relapse prevention treatment and vice versa—whether the relapse prevention treatment has a spillover effect on the quality of parent-child relationships.

The specific objectives are to:

Undertake an internal pilot to assess the recruitment and feasibility of delivering the treatment in a child and youth psychiatric clinic.Conduct a randomized control trial (RCT) to determine the effectiveness of relapse prevention on child and adolescent problem gaming and internet gaming disorder.Examine the moderating role of the parent-child relationship, including parent-child bonds and communication on the effect of relapse prevention on child and adolescent problem gaming and internet gaming disorder.Investigate the effect of completed relapse prevention treatment on parent-child relationshipsIntroduce a qualitative component to address:The subjective experiences of relapse prevention treatment among children and adolescents who took part in the program and their view of problematic gamingPerceived attitudes about parent-child relationships and parenting needs in carers whose children accomplished the relapse prevention treatmentThe feasibility of the treatment among clinicians who delivered the program

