**Objective:**

This study aims (1) to evaluate a relapse prevention treatment for patients showing signs of problem gaming or internet gaming disorder recruited from child and youth psychiatric clinics and (2) to test whether the quality of parent-child relationships plays a role in the effect of relapse prevention treatment and vice versa—whether the relapse prevention treatment has a spillover effect on the quality of parent-child relationships. Moreover, we explore the carer’s attitudes about parent-child relationships and child gaming, as well as experiences of the treatment among the children, their carers, and the clinicians who carried out the treatment.

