To date, there is no gold standard treatment for children and adolescents with internet gaming disorder. Cognitive behavioral therapy (CBT) is, however, often identified as a first-line treatment for problem gaming, offering patients help with recognizing triggers and cues for gaming, and for understanding and controlling their gaming behaviors [18]. A CBT-based form of treatment, relapse prevention [19,20], has been developed as a treatment for child and adolescent problem gaming and internet gaming disorder. The relapse prevention program, which includes 3 to 8 sessions, has a motivational and relapse-prevention approach [19] where the therapist explores the target, ie, the problem behavior of the individual. Such program is traditionally used as a tertiary (or indicated) intervention strategy, meaning that such preventive effort is used to alleviate the impact of an ongoing problem and to prevent more complications. Relapse prevention treatment is often provided in outpatient clinics, for reducing the likelihood of relapsing into addiction and substance abuse. It is considered among the most effective preventive efforts for substance addiction [20] and works by teaching the individual to identify both internal and external cues to prevent future relapses in similar situations. We hypothesize that by targeting these mechanisms, the treatment could also be effective in treating children and adolescents with problem gaming and internet gaming disorder, because of the similarities of these behavioral addictions to substance addiction.

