### Intervention

There is at this time a lack of consensus regarding treatment methods for problem gaming [22], in part due to a lack of clinical research [23]. However, together with 4 experienced psychologists in the field, we developed a manual drawing on previous knowledge in the field of addiction and the field of child and adolescent psychiatric treatment. Relapse prevention for alcohol and substance abuse was used as a theoretical underpinning [20] to develop a manual with 2 aspects in mind: adapting the blurbs and examples for children and adolescents—in part by including a fictionalized adolescent when demonstrating the theme of the particular session; and by structuring the sessions so that they could be easily adapted to fit the participant’s primary problem behavior—gaming or gambling. Patients who meet the criteria for disordered gambling or gaming (according to tentative criteria from the DSM-5) will be offered the opportunity to participate in a relapse preventive treatment intervention at their local clinic or where applicable at an adjacent clinic. The treatment will be administered in an individual format and consist of 7 to 9 sessions of 45 minutes over a period of 7 to 9 weeks. The treatment will be offered to participants both in person and via video link to facilitate participation for children and adolescents living further away from the participating clinics.

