### Measures and Data Collection

Background information, including gender, age, housing situation, and diagnosis, as well as primary outcome measures assessing gaming and gambling problems, will be collected via the platform “Blå appen” (“Blue application” in Swedish). Blå appen is a digital platform developed by the child and youth outpatient department in Region Skåne, distributing and summarizing online self-rated questionnaires. It is used throughout Swedish child and youth psychiatry to facilitate the usage of self-rated questionnaires to patients. The secondary outcome measures, including parent-child communication and connectedness and family climate, will be administered in paper format after the child has provided consent to the study. Because the secondary outcomes measures assess general parent-child interactions, specific questions about gaming will also be added. The patients who consent to the RCT will rate their gaming and gambling activity as well as their parent-child relationships before and after the treatment. The “treatment at usual” arm will do the rating of gaming and gambling activity as well as their parent-child relationships at the inclusion and 3 months after the inclusion to the study. The following primary outcome measures will be used:

The Game Addiction Scale for Adolescents [24] applies to gaming behavior during the previous 6 months based on 7 items. Each question covers one criterion in the DSM-5, answered on a 5-point Likert scale ranging from 1 (never) to 5 (very often) and should according to the developer be counted as endorsed when rated 3 or higher.The Diagnostic Screen for Gambling Problems–Control, Lying, and Preoccupation (NODS-CLiP) [25] is the shorter form of the NODS [26], which assesses gambling problems. NODS yield a score ranging from 0 to 10, corresponding to the DSM-4 criteria for gambling, where a score of 5 or more qualifies as pathological, a score of 3-4 corresponds to the subclinical syndrome of problem gambling, and scores of 1-2 corresponds to an “at-risk” status. NODS-CLiP comprises the 3 NODS items that best describe problem gambling, with 3 NODS questions pertaining to loss of Control, Lying, and Preoccupation—the “CLiP.”

The following secondary, somewhat adapted, outcome measures will be used:

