CBT-based forms of treatment, such as relapse prevention [19,20], typically used as a treatment for substance addiction [20], has been adapted to the treatment of child and youth problem gaming and internet gaming disorder. The goal of the treatment is to help the individual to identify both internal and external cues to prevent future relapses in similar situations. More specifically, the relapse prevention treatment is thought to help children to recognize triggers and cues for gaming, as well as to understand and control their gaming behaviors. Therefore, we hypothesize that by targeting these mechanisms, the treatment could be effective in treating children and adolescents with problem gaming and internet gaming disorder. As children are a part of a family system [16], it is likely that aspects of parent-child relationship, such as communication and emotional bonds, would have impact on child gaming behaviors [17]. Acknowledging parent-child relationships as being an important factor for child behavioral development, we hypothesize that the quality of parent-child relationships will play role for the effect of the treatment in a sense that the treatment will be more efficient for children reporting stronger parent-child bonds and communication. In addition, as children and parents interact in a dynamic manner [16], we also expect that the treatment will have spillover effect on parent-child relationships. We also have exploratory components to the projects. As previous research on user acceptability and satisfaction with relapse prevention as a treatment for problem gaming and internet gaming disorder is lacking, we explore how children and their carers, as well as clinicians who carried out the treatment, experience relapse prevention as a treatment for problem gaming and internet gaming disorder among children and youth. In addition, we also explore carers’ attitudes in terms of parent-child relationships before and after treatment of the child, as well as their reflections on potential parenting support needs in terms of their child’s gaming.

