### Limitations and Strengths

There are however some limitations to the study. The trial is not blinded, which may have an impact on both the patients’ behavior as well as clinicians’ practices. On the other hand, blinding does not necessarily ensure internal or external validity of the results [32], which is why we consider this limitation minor. As neuropsychiatric disorder is one of the major risk factors in problem gaming and internet gaming disorder [13], we expect that many of the patients included in the trial with be diagnosed with a neuropsychiatric disorder. This could be a potential limitation of the trial as the effect of the treatment may be affected by comorbidity in children with problem gaming or internet gaming disorder. Another possible limitation is the difficulty with recruiting patients as well as the potential dropout. Many children who game may not be aware of the problems that their gaming is imposing on their everyday lives, which is why they may not be likely to seek help or accept the given support. In addition, they may not be motivated to be engaged in the treatment. Therefore, we offer motivational sessions in the beginning of the treatment. Despite these limitations, there are several strengths to be noted. To our knowledge, this is the first RCT study testing the effect of relapse prevention on child and adolescent problem gaming and internet gaming disorder. As an increasing number of children engage in gaming [4,24], for some children, this activity may include significant problems [6,22] that would need attention from the clinics. Evaluating the efforts made by the clinics may provide more knowledge of the treatment of problem gaming in children. As problem behaviors in children interact with the family context, investigating parent-child relationships adjacent to the treatment of child problem gaming or internet gaming disorder is another important strength of the study. Further, this study includes a qualitative component involving different parties directly or indirectly involved in the treatment, ie, children, carers, and clinicians. Interviews with children, carers, and clinicians may help gaining knowledge of how the treatment is perceived by the individual who is directly involved in the treatment, the adults who take part in the child’s life on a daily basis, as well as the clinicians who are important stakeholders of the treatment.

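### The spillover objective is worded as the effect of completed treatment, whereas the aim and the hypothesis concern the treatment without that condition; followed literally, it opens the result to selection bias

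*Protocol article*

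**What the plan says.** The abstract gives the second half of the second aim as testing "whether the relapse prevention treatment has a spillover effect on the quality of parent-child relationships", and Aim and Objectives repeats this. The hypothesis under Expected Findings has the same scope: "we also expect that the treatment will have spillover effect on parent-child relationships".

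The list of specific objectives is narrower on this one item. The fourth is to "Investigate the effect of completed relapse prevention treatment on parent-child" relationships. Neither the effectiveness objective nor the moderation objective ("Examine the moderating role of the parent-child relationship, including parent-child bonds and communication on the effect of relapse prevention") carries the word *completed*.

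Under Measures and Data Collection, children who consent to the trial "will rate their gaming and gambling activity as well as their parent-child relationships before and after the treatment"; controls are rated at inclusion and 3 months later. No completion condition is attached to the ratings. Limitations and Strengths names dropout as a possible problem and says of the children that "they may not be motivated to be engaged in the treatment".

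**The concern.** Randomisation makes the two arms comparable as allocated. Completion of relapse prevention is observed only later and only in one arm. Children who finish may differ from those who stop in motivation, family support or otherwise, and the treatment-as-usual arm offers no matching subgroup. If the spillover result were estimated in completers, part of it could reflect who finished rather than what the treatment did.

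The outcome makes this more than a formality. The article expects children with stronger family bonds to do better in treatment. It does not say that bonds drive attendance, but that is a plausible inference, and selection would then act on the very thing being measured. At stake is whether the spillover finding can be read as an effect of relapse prevention.

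**Working it through.** **1. The passages side by side.**

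- Abstract (Objective), and the aim in Aim and Objectives: effect of the treatment; no completion condition.
- Effectiveness and moderation objectives: no completion condition.
- Spillover objective: effect of *completed* treatment.
- Hypothesis under Expected Findings: effect of the treatment; no completion condition.

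The word is probably not just a loose way of saying *after treatment*. The abstract's Methods paragraph, the objectives list and the Qualitative Component all use completing or accomplishing the treatment to select which carers are interviewed. The objectives list describes the children to be interviewed only as having taken part.

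**2. What a literal analysis could be.**

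- Completers versus controls: the arms are no longer comparable by design.
- Completers before and after (paired t tests are listed among the preliminary analyses): there is no control, so ordinary change over time counts as effect.
- A complier-type estimate: this keeps the randomisation, but the article does not specify one.

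**3. The plan's own figure.** The only sample size stated is 160 (80 + 80), for 40% versus 20% falling below the gaming cutoff. At two-sided 5% and 80% power (both assumed, since neither is stated), the pooled formula gives 82 per arm and the unpooled formula 79; power with 80 per arm is 79.4%. The figure is reproduced closely, but it concerns the primary outcome. No figure is given for the spillover objective, and below I use only the arm size of 80.

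**4. Illustration on follow-up levels, with no treatment effect.** The documents give no completion rate and no SD for the parent-child scales, so c and g are assumed.

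- c = share completing; g = completer minus non-completer difference at follow-up, in SD units.
- Completer mean minus whole-arm mean = (1 − c) × g.
- Examples: 0.3 × 0.4 = 0.12 SD; 0.4 × 0.6 = 0.24 SD.
- Comparing 80c completers with 80 controls: SE = √(1/(80c) + 1/80).
- Chance of a false positive at two-sided 5%: 1 − Φ(1.96 − bias/SE) + Φ(−1.96 − bias/SE).
- Worked case, c = 0.7, g = 0.5: bias 0.15; SE = √(1/56 + 1/80) = 0.174; false-positive rate 13.8%.

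| Completing (c) | Bias for g = 0.2 to 0.5 | False-positive rate |
|---|---|---|
| 0.9 | 0.02 to 0.05 SD | 5.2% to 6.1% |
| 0.8 | 0.04 to 0.10 SD | 5.7% to 9.2% |
| 0.7 | 0.06 to 0.15 SD | 6.4% to 13.8% |
| 0.6 | 0.08 to 0.20 SD | 7.2% to 19.5% |

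Comparing all 80 + 80 as randomised, with complete follow-up, gives bias 0 and 5%.

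**5. What baseline scores do to this.** Baseline relationship ratings are collected, and Statistical Analysis refers to pre- to postintervention change. Let g0 and g1 be the completer minus non-completer difference at baseline and follow-up, and b the slope of follow-up on baseline.

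- Change scores: bias = (1 − c) × (g1 − g0).
- Baseline-adjusted: bias = (1 − c) × (g1 − b × g0).
- With c = 0.7 and g0 = g1 = 0.4, the change-score bias is 0.3 × (0.4 − 0.4) = 0. The baseline-adjusted bias is 0.12 × (1 − b), which is small when scores are stable over time.

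The table is therefore an illustration for unadjusted follow-up levels. Material bias in change or adjusted analyses needs completers to develop differently over time for reasons other than treatment. Motivation is a candidate for that, but the documents give nothing to quantify it.

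**The case against.** The strongest reply is that this is one adjective in a condensed list. Every other statement of the spillover question is unconditional, ratings are planned for consenting trial patients in both arms, and the choice of analysis set is commonly left to a statistical analysis plan, which is not shown. That removes several stronger readings a reader might infer:

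- *That the plan compares completers with all controls.* No section sets that comparison or says that non-completers are left out.
- *That the second aim as a whole gives up the randomisation.* Its moderation half carries no completion condition.
- *That completers will have better scores and a spurious effect will be reported.* The rate and the difference are assumed, and a stable difference largely disappears once baseline is used.
- *That completion has no stable meaning because session counts conflict.* Background says "The relapse prevention program, which includes 3 to 8 sessions", with a literature citation. Intervention says the treatment will "consist of 7 to 9 sessions of 45 minutes over a period of 7 to 9 weeks", describing the manual developed for this trial. The two may describe different things. They should be reconciled in the text, but they do not by themselves show that completion is unstable in this trial.

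What the reply does not remove is the stated conflict. The point does not rest on a missing analysis set: the objective names a condition that the aim and hypothesis lack, and an analysis plan written from that objective would inherit it. It is true that a complier-average effect would fit the wording and keep the randomisation, but the reader cannot tell that this is meant.

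**Conclusion.** The point stands as an inconsistency in what the spillover objective sets out to estimate. As worded, it conditions on an event after randomisation that has no control-arm counterpart, in a trial that itself anticipates dropout and low motivation. Followed literally, it may give a result biased by selection. The size cannot be derived from the documents. With 60% to 90% completing and a difference of 0.2 to 0.5 SD (assumed), an unadjusted completers-versus-controls comparison would be off by 0.02 to 0.20 SD, with a false-positive rate of 5.2% to 19.5%. In change scores or with baseline adjustment the bias could be much smaller, or nil. The change is worth making because it is nearly free and closes this route to bias.

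**What to change.** Reword the objective as the effect of allocation to relapse prevention versus treatment as usual on parent-child relationships. Compare all randomised children by arm, with each subscale adjusted for its own baseline. Seek the follow-up ratings from every child regardless of completion, and state when a child who stops early is rated, since the intervention arm's second rating is described only as coming after the treatment.

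If an effect among completers is of interest, add a complier-average estimate with allocation as the instrument, labelled supplementary and with completion defined beforehand. Mplus, the software already named, can fit it. It assumes that allocation without completion has no effect on the outcome, which is debatable for children who attend part of the programme, so that assumption should be stated.

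The cost is a few words in the objective and the effort of following children who stop early. The estimated effect may be smaller than one among completers.

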## Methods

### Design

This study is a 2-arm, parallel-group, early-stage RCT with embedded qualitative components. The internal pilot will determine the recruitment and feasibility of the treatment. The recruitment start date is January 1, 2022, and the end date is December 30, 2022.

### Recruitment and Eligibility

The trial and the recruitment will be carried out in several outpatient child and youth psychiatric clinics in Region Skåne in southern Sweden. As part of routine practice, all children (ages 12-18 years) coming for their first visit to 4 child and youth psychiatric units in Region Skåne will be screened for gaming or gambling behaviors. Children will be eligible to be included in the trial if they are aged 12-18 years and referred to outpatient child and youth psychiatric clinics in Region Skåne, meet criteria for problem gaming and internet gaming disorder, and have capacity to provide written informed consent. Children below the age of 15 years need to have their caregivers’ consent. Children will be excluded if they do not speak Swedish. The clinicians who meet children during their first visit to the child and youth psychiatric unit will inform and invite the eligible children to participate in the study.

### Randomization

Participants will be randomized in a 1:1 ratio to either intervention or control. The study will include a total of 160 participants, applying a random allocation sequence using the “chit method” by preparing 160 chits of paper indicating either control or treatment [21]. Each patient will be allocated to a condition (control or treatment), and the chit will not be replaced if the patient drops out of the study. The allocation to treatment and control arms may thus be uneven at certain times during the trial, but the end result of randomization will result in an equal distribution between control and treatment. It will not be possible to blind participants, clinicians, or supervising researchers to randomization allocation. The control group will receive “treatment as usual” at their home clinic. For an overview of recruitment and randomization, see the flow diagram in Figure 1.

**Figure 1 figure1:**
[figure not shown]
Flow diagram. CYP: Child and Youth Psychiatric Clinic; CLiP: Control, Lying, and Preoccupation; GASA; Game Addiction Scale for Adolescents; RP: relapse prevention.

### Intervention

There is at this time a lack of consensus regarding treatment methods for problem gaming [22], in part due to a lack of clinical research [23]. However, together with 4 experienced psychologists in the field, we developed a manual drawing on previous knowledge in the field of addiction and the field of child and adolescent psychiatric treatment. Relapse prevention for alcohol and substance abuse was used as a theoretical underpinning [20] to develop a manual with 2 aspects in mind: adapting the blurbs and examples for children and adolescents—in part by including a fictionalized adolescent when demonstrating the theme of the particular session; and by structuring the sessions so that they could be easily adapted to fit the participant’s primary problem behavior—gaming or gambling. Patients who meet the criteria for disordered gambling or gaming (according to tentative criteria from the DSM-5) will be offered the opportunity to participate in a relapse preventive treatment intervention at their local clinic or where applicable at an adjacent clinic. The treatment will be administered in an individual format and consist of 7 to 9 sessions of 45 minutes over a period of 7 to 9 weeks. The treatment will be offered to participants both in person and via video link to facilitate participation for children and adolescents living further away from the participating clinics.

The treatment consists of three parts: (1) setting goals, (2) understanding and identifying high-risk situations and problem behaviors, and (3) consolidating the new activity schedule and identifying future high-risk behaviors. The first part is focused on examining the patient’s undesirable behavior, his/her motivation for change, and establishing goals with the treatment (this part primarily draws on motivational interviewing). This part of the treatment therefore varies between 1 to 3 sessions as participants may have different levels of motivation for changing their primary problem behavior, which is why some participants may require 1 or 2 extra sessions at the start of the treatment. The second part (drawing more from traditional CBT techniques) consists of exploring problematic situations using functional analysis; identifying high-risk situations and events, emotions, and cognitions that induce the problematic gaming behavior or result in a relapse; and managing game time with activity scheduling and practicing problem-solving skills. The final part consists of recognizing early warning signals that may indicate that the primary problem behavior is more likely to occur and consolidating the parts of the treatment that have been the most helpful in maintaining the new activity schedule.

Clinicians (psychiatrists and psychologists) with training in CBT will beforehand be educated in relapse prevention and will throughout the treatment be supervised by a clinician with vast experience of treating adults with gambling and gaming addictions.

